
### Biomarker levels

Sodium channel fragment levels are quantified using the Jess system (ProteinSimple, Bio-techne), a capillary-based automated Western blot platform. Plasma samples are resuspended in 0.1X Sample buffer (SimpleWestern, Bio-techne). Protein concentrations are determined using the DC Protein Assay (Biorad) to ensure consistent loading across all samples. Samples are prepared without reducing agents or heat denaturation to preserve protein integrity. Prepared plasma samples (3 µL) are loaded into the Jess assay plate along with controls, standards, and molecular weight ladders. Proteins are loaded into the capillary automatically (12–230 kDa range), electrophoresed and separated by size. A monoclonal anti-pan Nav antibody (Sigma-Aldrich, CAT#S8809, 1:500) targeting the α-subunit of human sodium channels is used for detection. This antibody, raised against the conserved intracellular III-IV loop peptide ‘CTEEQKKYYNAMKKLGSKK,’ was validated for specificity by immunoblotting in HEK293 cells transfected with Nav channels, showing selective detection of the native channel (~250 kDa) and its cleavage fragments, with no signal in untransfected controls [21]. The conserved sequence minimizes cross-reactivity. Chemiluminescence is used for signal detection. Quantitative data are captured by automated software, and protein band intensities are normalized to either a housekeeping protein or total protein for variability control. The native sodium channel (~250 kDa) and its lower molecular weight fragments are identified and quantified based on band intensity, facilitating the comparison of fragment expression across groups.

### Spasticity evaluations

Spasticity is assessed at M3 and M6 follow-up visits using the Modified Ashworth Scale (MAS), which grades muscle tone on a scale from 0 (no increase in muscle tone) to 4 (rigid muscle tone) [44]. This score measures the resistance perceived by the rater when passively moving a joint through its full range of movement. All evaluations are performed by a single, trained physiotherapist to minimize inter-observer variability. Associated phenomena, such as clonus and spasms, are also recorded to provide a comprehensive spasticity profile. Factors influencing variability (e.g., patient positioning, medication, and pain) are meticulously documented.

### Neurological Evaluations (GCS, ASIA)

**The Glasgow Coma Scale (GCS)** is a widely used, standardized tool for assessing consciousness in patients with TBI. It evaluates three key components: eye-opening, verbal, and motor responses, providing a rapid and reliable measure of neurological status. The Eye-Opening Response is scored from 4 to 1: 4 for spontaneous eye opening, 3 for a response to verbal stimuli, 2 for a response to painful stimuli, and 1 if there is no response. The Verbal Response evaluates the orientation and ability to communicate, scoring 5 for coherent and oriented speech, 4 for confusion, 3 for inappropriate words, 2 for incomprehensible sounds, and 1 for no vocalization. The Motor Response measures movement in response to commands or stimuli, scoring 6 for obeying commands, 5 for localizing pain, 4 for withdrawing from pain, 3 for abnormal flexion (decorticate posturing), 2 for abnormal extension (decerebrate posturing), and 1 for no response. The total GCS score ranges from 3 (deep coma) to 15 (full consciousness), allowing clinicians to classify the severity of brain injury and monitor changes in neurological status over time.

**The American Spinal Injury Association (ASIA) Impairment Scale** is a standardized framework for evaluating and classifying the severity of SCI [39,42]. It assesses sensory and motor functions across key dermatomes and myotomes, as well as sacral sparing, to determine the neurological level and completeness of the injury. Sensory evaluation tests light touch and pinprick sensations across 28 dermatomes bilaterally, from C2 to S4/S5. A cotton swab is used for light touch, and a safety pin for pinprick testing, with scores assigned as 2 for normal sensation, 1 for impaired sensation, and 0 for absent sensation. Special attention is given to the S4/S5 dermatome, as sacral sparing is critical for determining whether the injury is complete or incomplete. Motor function is evaluated by testing strength in 10 muscle groups corresponding to specific myotomes, ranging from elbow flexion (C5) to ankle plantar flexion (S1), scored from 5 (normal strength) to 0 (no contraction). Sacral motor function is further assessed by voluntary contraction of the external anal sphincter. The ASIA Impairment Scale assigns grades based on the completeness of the injury: Grade A indicates complete injury with no sensory or motor function preserved in sacral segments, Grades B-D reflect varying degrees of incomplete injuries with some preserved sensory or motor function below the injury level, and Grade E signifies normal sensory and motor function. The neurological level of injury is defined as the lowest spinal segment with intact sensory and motor function bilaterally.

### Functional Scales (GOS, GOSE, SF-36)

The **Glasgow Outcome Scale (GOS)** is a widely recognized tool for evaluating functional recovery following TBI [45]. It categorizes outcomes into five levels: death, vegetative state, severe disability, moderate disability, and good recovery. The GOS provides a high-level summary of a patient’s ability to reintegrate into daily life post-injury. To enhance its sensitivity, the **Glasgow Outcome Scale-Extended (GOSE)** subdivides each GOS category into upper and lower levels, offering a more nuanced evaluation of recovery trajectories. This refined scale is particularly beneficial for detecting subtle differences in functional outcomes, making it a valuable tool in clinical trials. Both the GOS and GOSE are exclusively applied to TBI patients in this study to monitor recovery.

The **Short Form Health Survey (SF-36)** is a generic quality-of-life questionnaire used for both SCI and TBI patients. It evaluates health-related quality of life (HRQoL) across eight domains, including physical functioning, pain, general health, vitality, social functioning, and mental health [46]. The SF-36 captures the broader impact of injuries and treatments on physical, emotional, and social well-being. Administered during follow-up visits, it complements the GOS and GOSE for TBI patients by offering additional insights into their quality of life. For SCI patients, it serves as a critical tool for assessing long-term functional impairments and evaluating the effectiveness of rehabilitation strategies.

### Pain assessments (VAS, DN4)

Pain assessments are critical for evaluating quality of life and rehabilitation in SCI and TBI patients. The **Visual Analogue Scale (VAS)** is a simple yet effective tool for quantifying pain intensity. Patients rate their pain on a 10-centimeter line, with anchors at “no pain” (0 cm) and “worst imaginable pain” (10 cm). This approach enables longitudinal tracking of pain severity, offering valuable insights into the effectiveness of therapeutic interventions over time. The **DN4 questionnaire (Douleur Neuropathique 4 Questions)** is specifically designed to identify neuropathic pain, which is prevalent among SCI patients [47]. It comprises 10 items: 7 symptom-related questions (e.g., burning, tingling, electric shocks) and 3 clinical examination items (e.g., hypoesthesia, allodynia). A score of ≥4 indicates the presence of neuropathic pain. Together, the VAS and DN4 provide a comprehensive evaluation of pain intensity and type, enabling targeted therapeutic strategies and effective monitoring of patient progress.

### Sphincter functions

Sphincter function is a crucial outcome in SCI patients, as SCI often compromise bladder and bowel control, significantly affecting quality of life. Assessments include bladder management (permanent or intermittent catheterization, normal urination) and bowel function (fecal incontinence, constipation), focusing on their impact on quality of life.

The **Table 3** summarizes the main data collected from the patients in the case report forms, from their inclusion in the study to the 6-month follow-up consultation.

**Table 3 pone.0319635.t003:** Main data collected from the patients in the case report forms, from their inclusion in the study to the 6-month follow-up consultation (ASIA: American Spinal Injury Association; GCS: Glasgow Coma Scale; BASIC: Brain and Spinal Injury Center [41]; AOSpine [39]; AIS: Abbreviated Injury Score; ISS: Injury Severity Score [48]; SAPS II: Simplified Acute Physiology Score II [49]; SOFA: Sepsis related Organ Faillure Assessment [50]; Kdigo [51]; modified Ashworth scale [44]; DN4 [47]; GOS: Glasgow Outcome Scale; GOSE: Glasgow Outcome Scale Extended [45]; SF36: Short Form 36 Health Survey [46]).

Inclusion	Hospital discharge	3 and 6-month follow-up
Background: -Gender -Age -Height -Weight Medical history: -Organ failure: heart, lung, kidney -Diabetes and chronic diseases -Cancer -Addiction: smoking, alcoholism	Spinal surgery: -Spinal stabilization -Spinal cord decompression -Levels Cranial surgery: -Intracranial lesion evacuation (craniotomy or craniectomy) -External ventricular drainage -Intracranial pressure monitoring Other surgery	Motricity: -Bed rest -Wheelchair use -Walking with assistance -Slow walking without assistance -Walking normally
Usual treatment: -Antiepileptic -Anticoagulant -Antihypertensive -Antidiabetic…	Additional treatments: -Analgesics -Antispasmodics -Antiepileptics -Antibiotics...	Additional treatments: -Analgesics -Antispasmodics -Antiepileptics -Antibiotics...
Trauma: -Date and time -Inclusion time -Type of accident	Intensive care stay: -Duration: stay, mechanical ventilation, sedation, intracranial pressure monitoring -Complications: refractory intracranial hypertension, infections (with treatment > 72 hours), septic shock, acute respiratory distress syndrome, acute renal failure (Kdigo > 3), cardiorespiratory arrest	Rehabilitation stay: -Medical complication -Specific support
Neurological evaluation: -ASIA score -GCS score	Neurological evaluation: -ASIA score -GCS score	Neurological evaluation: -ASIA score -GCS score
Clinical evaluation: -Heart rate -Blood pressure -Respiratory rate -Oxygen saturation	Spasticity: -Location -Modified Ashworth scale -Spasm, clonus -Treatment: antispastic, antiepileptic	Spasticity: -Location -Modified Ashworth scale -Spasm, clonus -Abnormal posture -Treatment: antispastic, antiepileptic
Pre-hospitalization management: -Cardiopulmonary arrest -Hypovolemic shock -Fluid restoration -Vasopressor treatment	Pain: -Location, duration, frequency -Visual analogue scale -DN4 -Treatment: analgesic, antiepileptic Sphincter functions: -Permanent bladder catheterization -Iterative bladder catheterization -Normal urination -Fecal incontinence -Constipation	Pain: -Location, duration, frequency -Visual analogue scale -DN4 -Treatment: analgesic, antiepileptic Sphincter functions: -Permanent bladder catheterization -Iterative bladder catheterization -Normal urination -Fecal incontinence -Constipation Functional scales: -GOS, GOSE -SF36
Spinal cord injury: -Level -BASIC score -AOSpine vertebral fracture type Traumatic brain injury: -Intracranial lesions -Rotterdam score		
Trauma scores: -AIS and ISS -IGS2 and SOFA		
Biology: -Renal clearance -Hepatic function -Hemoglobin -Lactate	Biology: -Renal clearance -Hepatic function -Hemoglobin	Biology: -Renal clearance -Hepatic function -Hemoglobin

### Justification of sample size

The study includes a total of 40 participants distributed as follows: 20 patients with spinal cord injury (SCI), 10 patients with traumatic brain injury (TBI), and 10 healthy controls. The selection of 20 SCI patients is based on the annual admission rates for SCI at the study institution, ensuring a representative sample of the population served. The inclusion of 10 TBI patients is justified to account for potential confounding factors arising from the overlapping but distinct injury mechanisms of SCI and TBI. Furthermore, 10 healthy controls are included to provide a robust baseline for sodium channel fragment levels, facilitating a balanced comparison across the three groups.

This sample size is sufficient to detect meaningful trends and associations between sodium channel fragments and clinical outcomes, including spasticity, while maintaining feasibility within the scope of a pilot study. The findings will generate preliminary evidence regarding the diagnostic and prognostic utility of sodium channel fragments in neurological injuries and will guide the design of larger-scale clinical trials.

Given the exploratory nature of this study, no formal interim analyses are planned. As the trial involves minimal-risk procedures, such as blood sampling, no pre-specified stopping rules have been established. In the event of significant deviations from the protocol or unforeseen safety concerns, the trial steering committee will consult the Ethics Committee to determine whether adjustments or study termination are necessary. All such decisions will be transparently documented and communicated to relevant stakeholders, including regulatory authorities, to ensure compliance with ethical standards.

### Randomisation, blinding

The SpasT-SCI-T trial is an observational study employing a case-control and cohort design; therefore, randomization is not applicable. Participants are allocated to groups based on predefined eligibility criteria rather than random assignment. Consequently, sequence generation, allocation concealment, and implementation of randomization do not apply to this trial. To mitigate bias and maintain data integrity, laboratory personnel conducting biochemical analyses remain blinded to group allocation. This blinding ensures that sodium channel fragment quantification is performed without preconceived assumptions about the samples, enhancing the reliability and validity of the results.

### Statistical methods

The primary objective of this study is to quantify sodium channel fragments in blood samples and compare their levels across the three participant groups: healthy controls (Group 1), SCI patients (Group 2) and TBI patients (Group 3). To address this objective, statistical analyses will begin with group comparisons.

1**Group Comparisons:** For normally distributed data, one-way analysis of variance (ANOVA) will be employed to identify differences in sodium channel fragment levels among the three groups. If data are not normally distributed, the Kruskal-Wallis test will be applied as a non-parametric alternative. Post-hoc analyses will follow these tests to assess pairwise comparisons, using Tukey’s test for ANOVA or the Mann-Whitney U test for non-parametric data.2**Effect Size Calculation:** Effect sizes (e.g. Cohen’s d for t-tests or η² for ANOVA) will be calculated to quantify the magnitude of differences between groups.

For secondary outcomes, analyses will focus on the temporal kinetics of sodium channel fragments and their correlation with clinical outcomes.

1**Temporal Kinetics:** Changes in fragment levels over time, measured at baseline (6 hours), during the acute phase (Days 1, 3, 5, 7), and at follow-up (Months 3 and 6), will be analyzed using repeated-measures ANOVA for normally distributed data. For non-normally distributed data, the Friedman test will be used. Bonferroni corrections will be applied during multiple comparisons.2**Spasticity Correlation:** The relationship between sodium channel fragment levels and spasticity severity in SCI patients will be assessed using Spearman’s rank correlation coefficients, with spasticity evaluated at Months 3 and 6 using the Modified Ashworth Scale (MAS).3**Subgroup Analysis (SCI Severity):** Subgroup analyses will investigate whether sodium channel fragment levels differ by injury severity. In SCI patients, severity will be categorized based on the American Spinal Injury Association (ASIA) Impairment Scale grades (A–D). Similarly, spasticity onset will be analyzed as a binary outcome (presence vs. absence). For TBI patients, the Glasgow Coma Scale (GCS) will be used to classify injury severity, enabling comparisons of sodium channel fragment levels across defined severity subgroups.

Additional statistical methods will include multivariable linear regression models to adjust for potential confounders, including age, sex, injury severity (ASIA grades A–D for SCI, GCS scores for TBI), and concurrent medications (antispasmodics, analgesics, antiepileptics) as primary factors, as well as additional variables from Table 3 such as comorbidities (diabetes, organ failure), trauma context (type of accident), and biological parameters (hemoglobin, renal clearance) where statistically significant or clinically relevant, informed by prior literature [14,21]. This ensures that observed associations between sodium channel fragment levels and outcomes such as spasticity are robust and not influenced by baseline characteristics. Receiver operating characteristic (ROC) curves will be generated to identify threshold levels of sodium channel fragments that differentiate SCI from TBI or predict spasticity onset. To address missing data, multiple imputation methods will be applied, minimizing bias and preserving the validity of the analyses.

Continuous variables will be expressed as means with standard deviations for normally distributed data or medians with interquartile ranges for non-normally distributed data. Categorical variables will be summarized as frequencies and percentages. For all primary and secondary analyses, a two-tailed p-value < 0.05 will be considered statistically significant. Patients who die before the 3-month follow-up will be excluded from spasticity-related analyses due to insufficient time for spasticity development, but all data collected up to the time of death will be included in secondary analyses, such as demographic characterization and early biomarker levels.

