### Study design

The SpasT-SCI-T study is a prospective, multicenter observational trial performed in France. The study employs a combination of case-control and cohort designs to address its primary and secondary objectives. The inclusion of patients will officially begin on March 17, 2025 and end on September 20, 2026. A total of 40 participants are recruited, divided into three groups:

1**Group 1 (Healthy Controls):** Ten healthy volunteers provide baseline blood samples for comparison.2**Group 2 (SCI Patients):** Twenty patients with acute traumatic SCI confirmed by imaging and no associated TBI.3**Group 3 (TBI Patients):** Ten patients with acute TBI confirmed by imaging and no associated SCI.

The trial consists of three phases:

1**Inclusion Phase:** Participants are enrolled into one of the three study groups based on predefined eligibility criteria.2**Acute Phase (0–14 days):** This phase focuses on the immediate response to trauma, capturing rapid changes in sodium channel fragment levels during the critical early period. Blood samples are collected within 6 hours post-trauma and at multiple time points (Days 1, 3, 5, 7, and 14) to monitor early biomarker kinetics.3**Late Follow-Up Phase (3 and 6 months):** The late follow-up phase assesses long-term changes in sodium channel fragment levels and their association with recovery trajectories and clinical outcomes, including the onset and severity of spasticity. Blood samples are collected during follow-up consultations at 3 and 6 months post-trauma. A 6-month follow-up was selected as clinical signs of spasticity typically stabilize between 2 and 6 months post-injury, with electrophysiological measures showing minimal change thereafter [38].

The CONSORT diagram in Fig 1 provides details on the timeline for enrollment, interventions, and assessments across the participant groups, while the overall study design is summarized in Fig 2.

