#### Group 2: Spinal Cord Injury (SCI) patients.

SCI patients are prospectively recruited from the Intensive Care Unit or Neurosurgical Department at Hôpital Nord within 6 hours post-trauma. Upon admission, interventions for these patients begin with clinical and imaging assessments. A computed tomography (CT) scan is performed on admission to confirm vertebral fractures or spinal column instability. Magnetic resonance imaging (MRI) provides detailed characterization of the SCI, documenting patterns such as contusion, compression, hemorrhage, or edema. Injury severity is further classified using the AOSpine fracture classification [39] and BASIC scoring system [40,41].

Baseline neurological status is documented using the American Spinal Injury Association (ASIA) Impairment Scale, which evaluates the severity and level of the SCI [39,42]. Additional documentation includes respiratory and hemodynamic stability, renal clearance, liver function, and hemoglobin levels.

Blood sampling begins with a 4 mL venous sample collected within the 6 hours of trauma. Additional samples are collected during the acute phase on days 1, 3, 5, 7 and 14 to monitor early biomarker kinetics. Further samples are obtained at 3 months (M3) and 6 months (M6) post-trauma, offering insights into long-term biomarker dynamics. As part of the follow-up interventions, at M3 and M6, spasticity is assessed using the **Modified Ashworth Scale** (MAS, Table 2), alongside detailed evaluations of neurological recovery and residual deficits. These assessments are complemented by documentation of neurological recovery and residual deficits, enabling correlations between clinical outcomes and sodium channel fragment levels.

**Table 2 pone.0319635.t002:** Modified Ashworth scale for spasticity assessment [44].

Modified Ashworth score	Clinical findings
0	No increase in muscle tone
1	Slight increase in muscle tone, with a catch and release or minimal resistance at the end of the range of motion when an affected part(s) is moved in flexion or extension
1+	Slight increase in muscle tone, manifested as a catch, followed by minimal resistance through the remainder (less than half) of the range of motion
2	A marked increase in muscle tone throughout most of the range of motion, but the affected part(s) are still easily moved
3	Considerable increase in muscle tone, passive movement difficult
4	Affected part(s) rigid in flexion or extension

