#### Group 3: Traumatic Brain Injury (TBI) patients.

Interventions for TBI patients are tailored to intracranial trauma and are similar in structure to those for SCI patients, with modifications to address brain injury specifics. A whole-body CT scan is performed upon admission to confirm intracranial hemorrhage and exclude SCI, ensuring group specificity. Neurological status is assessed using the Glasgow Coma Scale (GCS) to document the severity of brain injury [43]. Trauma-related data, including respiratory and hemodynamic stability, renal clearance, liver function, and hemoglobin levels, are recorded. Blood sampling begins with a 4 mL venous sample collected within the 6 hours of trauma during the routine biological workup. Additional samples are obtained during the acute phase at Days 1, 3, 5, 7 and 14 to capture early biomarker dynamics. Further samples are collected during late follow-up visits at M3 and M6 to evaluate the longer-term biomarker behavior. General neurological assessments are performed at M3 and M6 to evaluate recovery. These outcomes are correlated with sodium channel fragment levels to explore potential biomarker-based prognostication.

For SCI and TBI patients (Groups 2 and 3), detailed records of all medical treatments administered during hospitalization will be maintained. This includes, but is not limited to: anticoagulation therapy, antibiotic regimens, anti-spastic medications, and pain management protocols. This documentation allows for the evaluation of potential confounding factors and ensures that biomarker changes can be interpreted in the context of treatment.

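### The temporal-kinetics analysis leaves out the scheduled Day 14 sample and names tests that cannot use the partial series of patients who die

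*Protocol article*

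**What the plan says.** The sampling schedule is consistent across the protocol article. Study design defines an acute phase of 0 to 14 days, with a draw within 6 hours and then "at multiple time points (Days 1, 3, 5, 7, and 14) to monitor early biomarker kinetics". The SCI section says "Additional samples are collected during the acute phase on days 1, 3, 5, 7 and 14 to monitor early biomarker kinetics", and the TBI section says "Additional samples are obtained during the acute phase at Days 1, 3, 5, 7 and 14 to capture early biomarker dynamics". The Fig 2 legend and the intensive care entry under Sites and ressources give the same days. With Months 3 and 6, this makes eight samples per injured patient.

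The Temporal Kinetics item under Statistical methods is the only place that says how these series are analysed. After the 6-hour baseline it reads: "during the acute phase (Days 1, 3, 5, 7), and at follow-up (Months 3 and 6), will be analyzed using repeated-measures ANOVA". It continues: "For non-normally distributed data, the Friedman test will be used", and "Bonferroni corrections will be applied during multiple comparisons". It gives seven times and no reason for leaving out Day 14. It does not name a follow-up test or a set of comparisons, and it does not say whether SCI and TBI are analysed separately.

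Later in the same section, multiple imputation is planned for missing data in general terms. Patients who die before Month 3 are removed from the spasticity analyses. Their data up to death are to be kept in secondary analyses, with early biomarker levels given as an example.

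**The concern.** Characterising the kinetics in SCI and TBI is the first secondary objective. A sample drawn from every injured patient for that purpose is absent from the stated analysis. It is also the only observation between the end of the first week and Month 3, so the stated analysis has no information on when levels fall or whether they persist in that interval.

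The second issue is the choice of test. Classical repeated-measures ANOVA and the Friedman test need a complete row for each patient. The patients have acute trauma, the TBI group enters with a GCS of 13 or less, and follow-up runs to six months. The article itself anticipates deaths before Month 3. A test that cannot use a partial series sits badly with an instruction to keep what was observed before death.

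**Working it through.** The article gives no effect size, dropout rate or adjusted alpha for this analysis, so there is no figure of its own to reproduce.

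**1. Schedule against analysis list**

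| | 6 h | D1 | D3 | D5 | D7 | D14 | M3 | M6 | Total |
|---|---|---|---|---|---|---|---|---|---|
| Scheduled draws | x | x | x | x | x | x | x | x | 8 |
| Kinetics analysis | x | x | x | x | x | – | x | x | 7 |

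With 20 SCI and 10 TBI patients, 30 × 8 = 240 samples are scheduled. The 30 Day 14 samples (1/8 = 12.5%) are not in the kinetics list.

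**2. Death and the partial series**

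A patient who dies between Day 7 and Month 3 can have at most five of the seven listed values. Neither named test can use those five without Month 3 and Month 6 values, and these do not exist. Each such death removes one patient in ten from the TBI group, or requires levels to be imputed after death.

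**3. Complete series if imputation were not applied**

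Assumption: each sample is missing independently with probability m. The share of patients complete on k times is (1 − m)^k.

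| m (assumed) | k = 7, as listed | SCI of 20 / TBI of 10 | k = 8, with Day 14 | SCI of 20 / TBI of 10 |
|---|---|---|---|---|
| 5% | 0.95^7 = 0.698 | 14.0 / 7.0 | 0.95^8 = 0.663 | 13.3 / 6.6 |
| 10% | 0.90^7 = 0.478 | 9.6 / 4.8 | 0.90^8 = 0.430 | 8.6 / 4.3 |

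These counts show how heavily the named tests depend on imputation. They do not forecast the analysed sample.

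**4. Conditional side check on the Bonferroni rule**

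Assumptions, all needed together: the non-normal branch, TBI analysed alone, all pairs of times compared, and exact Wilcoxon signed-rank follow-up tests. The smallest two-sided exact p with n pairs is 2/2^n. This is 0.00195 at n = 10, 0.00391 at n = 9 and 0.00781 at n = 8.

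- Seven listed times: 7 × 6/2 = 21 pairs, and 0.05/21 = 0.00238. Significance is only just possible with all 10 patients complete, and impossible with 9.
- Eight times: 8 × 7/2 = 28 pairs, and 0.05/28 = 0.00179. Significance is impossible even with 10.
- Eight times, each later time against 6 h only: 0.05/7 = 0.00714. Significance is possible with 10 or 9 pairs, but not with 8.

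The SCI group is not affected (smallest p about 0.000002 at n = 20). Paired t-tests and Dunn-type rank comparisons do not meet this floor.

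**The case against.** The strongest reply is that only the Day 14 mismatch is an outright error, and that it is one item in a secondary analysis of a self-described pilot. That is fair as to scale. It does not remove the point, because the article states both lists and they disagree, whatever a separate analysis plan might add.

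On missing data, a reader might infer that the kinetics would be run only on survivors with every draw. The document does not support that: it plans multiple imputation and wants data up to death retained. Nor does it say that levels after death would be imputed. What stands is narrower. The named tests give no way to honour both statements for a patient who dies, and after imputation the Friedman statistic has no simple pooling rule. General rules for pooling chi-square statistics exist, but they are crude with 10 patients.

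On multiplicity, a reader might infer that the Bonferroni rule makes significance impossible in TBI. The document never says that all pairs are compared, and it names no follow-up test to Friedman. The result needs all four conditions in the side check. Even then, the seven times as written leave significance just attainable with 10 complete patients; outright impossibility at n = 10 appears only once Day 14 is restored. The follow-up test and the set of comparisons may properly be left to the unseen analysis plan.

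A mixed model is not free of difficulty either. It rests on missing at random, and its late means extend implicitly past death unless their interpretation is stated.

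**Conclusion.** The Day 14 omission holds without any assumption: eight samples are scheduled, seven are listed for analysis, and no reason is given. The sample left out is the only one between Day 7 and Month 3.

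The point about the tests holds in limited form. Repeated-measures ANOVA and Friedman cannot use a partial series. Imputation covers occasional missed draws but not levels after death, and this conflicts with keeping data up to death in secondary analyses. The 70% and 48% complete-series figures (66% and 43% with Day 14) rest on assumed, independent missingness of 5% and 10%, and apply only if imputation is not used.

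The Bonferroni arithmetic is a conditional caution, not an established defect. Its practical use is as a warning: adding Day 14 while keeping an all-pairs signed-rank approach in 10 TBI patients would create a floor that no effect could pass.

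**What to change.** 1. Add Day 14 to the times listed under Temporal Kinetics, so that the analysis matches the schedule. This costs nothing, since the sample is already drawn.
2. Replace repeated-measures ANOVA and Friedman for this objective with a linear mixed model on all observed samples: group (SCI, TBI) by time, a patient random effect, and small-sample degrees of freedom. State that the Month 3 and Month 6 estimates are to be read as applying to patients alive at those visits. If logs are used, say how undetectable bands are handled, because detection is itself part of the primary outcome.
3. Preferably, limit the comparisons to pre-set contrasts of each later time against the 6-hour sample, which is seven contrasts with Day 14 included. If a rank version is kept, note that it still needs at least 9 complete pairs for a contrast to reach 0.05/7. At an assumed 10% missing per sample, TBI would have on average 10 × 0.9 × 0.9 = 8.1 pairs, so this eases the floor without removing it.

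The change is to analysis wording only, with no new patients, visits or samples. The price is a missing-at-random assumption, a stated interpretation after death, and a choice of scale.
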